### Research question and study objectives

#### Research question

How does an optimised implementation model influence the appropriate coverage of pneumonia management among under-five children, and what clinical, behavioural and system-level factors shape treatment outcomes, adherence and gender-related care-seeking patterns?

#### Primary objective

To develop, refine, implement and evaluate an optimised, sustainable and scalable implementation model for improving population-based coverage of pneumonia management among under-five children, in alignment with the GoI’s Childhood Pneumonia Management Guidelines.^4^ The model aims to achieve ≥80% treatment coverage in the target population.

#### Secondary objectives

To assess the proportion of children who recover after 7 days of treatment.To estimate the proportion of treatment failures among diagnosed pneumonia cases.To measure compliance with the recommended pneumonia treatment protocol.To determine the proportion of children who complied with hospital referral advice.To document the duration and treatment details of inpatient pneumonia cases.To explore the knowledge, perceptions and experiences of caregivers, healthcare providers and community health workers regarding pneumonia identification, referral and management.To identify barriers to and facilitators of equitable pneumonia treatment, particularly among girl children, in the context of the ‘Save the Girl Child’ initiative.

Additionally, the household level and facility level cost for management of the pneumonia cases before and after implementation of the guideline using the optimised model will also be collected by the research team.

## Methods and analysis

### Study design

This implementation study includes a mixed-method approach aiming to scale up the management of under-five pneumonia and uses a quasi-experimental pre-post design. Our approach involves a non-sequential, repeated, cyclical and iterative implementation process, characterised by a series of overlapping cycles that involves implementation, process learning with both quantitative and qualitative feedback and ongoing quantitative coverage evaluation.^12^ Regular meetings in collaboration with government officials will provide a platform for deliberation on the implementation progress, the insights acquired, the assessment of model performance and the continuous enhancement of the implementation process.^12^

### Implementation science framework

We will employ a flexible and adaptive strategy, actively engaging relevant stakeholders, thoroughly examining contextual factors, identifying implementation barriers and facilitators, allocating essential resources as needed and establishing a continuous monitoring system. These components collectively contribute to our aim of ensuring the success and sustainability of this guideline, embodying key elements of a robust implementation framework.^12^

### Operational definitions

In this, pneumonia is defined as the mother/caregiver reporting any episode of cough along with either fast breathing or difficult breathing or stridor (‘khar khar’ or ‘khad khad’) or chest indrawing or pneumonia (‘pasliyon ka chalna’) or any danger signs (eg, axillary temperature <35.5 or ≥37.5 °C or not able to feed or convulsion or movement only when stimulated or no movements at all among children aged less than 59 days and inability to breastfeed or drink or vomits everything or lethargy or reduced level of unconsciousness or convulsions among children ageing 2–59 months) in the last 28 days.^4^ In a low-resource setting like India, grassroots-level workers like ASHAs and caregivers, sometimes non-literate, are the ones reporting cases of pneumonia to the health facility. In this context, it is challenging to employ a definition of pneumonia that requires access to laboratory or radiological examinations. Considering the existing capacity of the health services, we need to employ a definition that is based on clinical signs that can be recognised by caretakers or ASHAs.^5^ Hence, the definition of under-five pneumonia, in this study, is broad (with low specificity) for operational reasons. Additionally, this operational definition has been employed in other studies which were conducted in similar settings in India.^5^

### Study setting

The study will be conducted in the Palwal district, located in the northern Indian state of Haryana, and covers an area of 1359 square kilometres, including three administrative divisions known as tehsils: Palwal, Hodal and Hathin^13^ (figure 1). It comprises 282 villages, 237 Gram Panchayats, one municipal council, two municipal committees, three subdivisions and four development blocks and is located approximately 80 km from the capital of India. This district serves a population of 1 273 665 through one District Hospital (DH), seven Community Health Centres (CHCs), 26 Primary Health Centres (PHCs), 49 functional HWCs and 1108 Anganwadi centres. The PHCs target to serve around 49 000 people each, with 10 subcenters catering to about 12 000 to 13 000 people each.^13^ The district has 37 medical officers at CHCs and PHCs, 176 medical officers and other healthcare professionals at the district hospital. The average literacy rate is 69.32%, and 12% of the population is under five years of age with an annual birth rate of 25 per 1000 population.^13 14^

**Figure 1 F1:**
[figure not shown]
Map of the study area.

The catchment area for our implementation research will be the HWCs of Palwal district. The HWCs were established under the Aayushman Bharat—Haryana Health Protection Mission, and currently, 49 are functional in the Palwal district to provide comprehensive primary healthcare services in proximity to residents’ homes.^14^

The district health authorities will determine the number of HWCs to be assessed from 49 functional centres and subsequently share the list with the research team. After the preliminary assessment, the research team will select ten HWCs for inclusion in the study (figure 1). We will exclude HWCs that lack appropriate infrastructure and human resources, as these are basic prerequisites for implementing the intervention. Specifically, HWCs must have a functional building, essential utilities such as electricity and water supply, and basic furnishings. Additionally, the presence of adequate human resources to deliver comprehensive primary healthcare services is critical. HWCs should also be operational on a regular basis. Facilities that do not meet these criteria would require significant upgrades, which may be time-consuming and not feasible within the study period. Among the eligible facilities, preference will be given to HWCs that are reasonably accessible (within approximately 11–12 km) from the DH to facilitate referral linkages and supervision.

Furthermore, in addition to the selected HWCs, the research team will conduct other facility assessments (PHCs, CHCs and DH) that cater to the population referred from these HWCs. The catchment area of this study will have an estimated population of 1,07,440, consisting of 42 villages and 9897 under-five populations.^13^

### Eligibility and inclusion criteria

The mothers/primary caregivers of the under-five children and healthcare workers in the facility and community within the catchment area will be included in this study.

### Sample size

A recent study in the same district found that the prevalence of pneumonia among under-five children in the last 2 weeks was around 5%.^15^ Currently, approximately 25% of under-five children seek appropriate care for ARI, indicating a programme coverage of around 25%.^5 16^ With the introduction of the new implementation strategy, we expect an increase in pneumonia treatment coverage by 80%. To account for potential non-response and to estimate 80% coverage of appropriate treatment at baseline and end-line surveys for under-five children with pneumonia cases (as per the operational definition), a conservative sample size of 120 is to be included. Additionally, based on these assumptions, the estimated sample size at a 5% level of significance for each survey (baseline and end-line), and a varied range of coverage is shown in figure 2.

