**Figure 2 F2:**
[figure not shown]
Sample size estimation.

The total number of children to be surveyed is calculated based on a prevalence rate of 5%, resulting in an estimated sample size of 2400.^5^ Considering the proportion of 5-year-olds in the population (12% based on census data) and the average household size (4.8 as per the NFHS 5 report for Haryana), the number of households to be covered is calculated as 4167 households.^17^ These households will be selected using Probability Proportional to Size (PPS) sampling methods from the defined study area served by the 10 HWCs.^18^ Since community-level healthcare workers maintain a list of under-five children in each household, systematic random sampling will be used to select children within the chosen households.

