### Description and tracking process of study outcomes

The primary targeted outcome of this study is achieving ≥80% coverage of appropriate pneumonia management and will be assessed using a structured quantitative household survey tool. Three cross-sectional surveys (baseline, midline and endline) will be conducted with caregivers of under-five children who experienced pneumonia-like symptoms in the previous 28 days. These surveys will capture whether care was sought from appropriate sources and whether treatment received aligned with the national guidelines. The success of this research will be when at least 80% of these children:

Received care from appropriate sourcesWere managed according to the recommended national protocols with ≥80% compliance to the prescribed treatment.

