The research findings from the learning block will be used to enhance Model 0+, leading to the development of Model 1. Subsequently, a series of rapid cycles involving concurrent implementation, monitoring and strategy refinement will be conducted in the remaining six HWCs. These iterations will take place in multiple co-design workshops, with significant involvement from government authorities. The iterative process will continue until an optimised and comprehensive strategy/model is achieved with the potential for achieving high coverage and quality of pneumonia management among under-five children in the study areas (figure 4). The model will be considered optimised when the healthcare providers can consistently recognise pneumonia signs and symptoms and manage cases in accordance with the national guidelines, with ≥80% fidelity among the suspected cases visiting the centres. Second, treatment compliance among under-five children reaches at least 80%, who have received this treatment from the health facilities.

Once the model is optimised, it will be scaled up to all ten HWCs in the study area. During this scale-up phase (estimated to last 7–8 months), we will continue to monitor both implementation barriers and quantitative indicators such as fidelity to the guidelines and treatment compliance. At the conclusion of the scale-up phase, an endline household survey will be conducted using PPS sampling to identify 120 under-five children who had pneumonia symptoms in the past 28 days. These data will be compared with baseline measurements to assess changes in key outcome indicators, i.e. under-five pneumonia cases receiving management (as per the national guidelines) from the appropriate health facilities, which determines the coverage of appropriate pneumonia management.

The final findings will be shared with state- and district-level health authorities in Haryana. If the district government expresses interest and supports the approach, the model, having already been scaled up within the study area, may be adopted for implementation across the entire Palwal district, with continued technical support from the research team.

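### The 2400 children and 4167 households rest on a 2-week prevalence of 5%, but cases are counted over 28 days, so this survey size does not correspond to about 120 cases

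*Protocol article*

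**What the plan says.** The first paragraph of Sample size takes its prevalence from an earlier study in the same district: "the prevalence of pneumonia among under-five children in the last 2 weeks was around 5" per cent. For cases meeting the operational definition it then says that "a conservative sample size of 120 is to be included". The paragraph after Figure 2 describes the number of children as "calculated based on a prevalence rate of 5%, resulting in an estimated sample size of 2400". With an under-five share of "12% based on census data" and a mean household size of "4.8 as per the NFHS 5 report for Haryana", it concludes that "the number of households to be covered is calculated as 4167 households". The Abstract repeats this chain of households, children and cases.

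The case window is different. Operational definitions counts episodes in the last 28 days. Description and tracking process of study outcomes says that the baseline, midline and endline surveys concern children "who experienced pneumonia-like symptoms in the previous 28 days". Implementation strategy describes the endline survey as one "to identify 120 under-five children who had pneumonia symptoms in the past 28 days".

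Study setting gives the catchment a population of 107,440, including 9897 under-fives.

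**The concern.** The number of children to screen is the target number of cases divided by the proportion of children who will count as cases. That proportion must refer to the same recall window as the case definition. Here the divisor is a 14-day prevalence and the count runs over 28 days. A window twice as long normally catches more children, so 2400 children and 120 cases do not belong together.

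Two things are at stake. The article misstates the expected number of cases for the primary coverage outcome. It also describes the endline survey in two ways, as a fixed set of households and as a search for 120 cases. These agree only if the 28-day yield really is 5%, and the article does not say which governs if the count passes 120 early.

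**Working it through.** **Inputs from the article.** Target of 120 cases; prevalence 5% over 2 weeks; under-five share 12%; household size 4.8 (all Sample size). Case window of 28 days (Operational definitions, Description and tracking process, Implementation strategy). Catchment population 107,440 with 9897 under-fives (Study setting).

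**Inputs assumed.** Mean episode duration D of 0 to 14 days, steady incidence, and recall loss in the earlier fortnight of 0 to 50%. The article gives none of these.

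**1. Reproduce the plan.**
- Children: 120 / 0.05 = 2400.
- Households: 2400 / (0.12 × 4.8) = 2400 / 0.576 = 4166.7, rounded up to 4167.

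Both match, so the arithmetic is right and the fault lies in the input.

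**2. Rescale the prevalence to 28 days.** With steady incidence, period prevalence over a window W is incidence × (W + D). The 28-day prevalence is therefore 5% × (28 + D) / (14 + D).

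| D (days) | 28-day prevalence | Cases in 2400 children | Children for 120 cases |
|---|---|---|---|
| 0 | 10.0% | 240 | 1200 |
| 7 | 8.3% | 200 | 1440 |
| 14 | 7.5% | 180 | 1600 |

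Two checks by other routes:
- Independent fortnights, counting each child once: 1 − 0.95² = 9.75%, or 234 cases.
- Half of the earlier fortnight's cases forgotten: 5% + 2.5% = 7.5%, or 180 cases.

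The figure stays at 5% only if the earlier fortnight adds no cases.

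**3. Use the catchment's own under-five share.**
- Share: 9897 / 107,440 = 9.2%.
- Children in 4167 households: 4167 × 4.8 × 0.0921 ≈ 1842.
- Cases: 1842 × 0.075 ≈ 138, up to 1842 × 0.10 ≈ 184. At 5%: 1842 × 0.05 ≈ 92.

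**4. What follows if only the prevalence is corrected.** Keeping 12%, 120 cases would appear to need 1600 / 0.576 ≈ 2778 households at 7.5%, or 1200 / 0.576 ≈ 2084 at 10%. At a 9.2% share those households hold about 1228 and 921 children, and each gives about 92 cases (1228 × 0.075; 921 × 0.10).

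**5. Effect on precision.** The 95% half-width at 80% coverage, ignoring clustering, is 1.96 × √(0.16 / n): 7.2 points with 120 cases, 5.8 with 180 and 5.1 with 240. With 138 and 184 cases it is 6.7 and 5.8 points.

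**The case against.** The strongest reply is that the error is harmless to inference. It gives more cases than planned, so power and precision are safe and there is some room for clustering. This stands, and it limits the seriousness of the point.

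Second, the excess is smaller than the prevalence alone suggests, because the 12% share is too high for this catchment. This also stands. It narrows the range to 138 to 184 cases, and 4167 households would give 120 cases only at a prevalence of about 6.5% (120 / 1842). One input partly offsetting another is still not a stated justification.

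Third, the 5% in the paragraph after Figure 2 carries a different citation from the 5% in the paragraph before it, so its window could differ. The article states no other window, and two weeks is the only one it attaches to this figure. Figure 2 itself could not be read.

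Fourth, the size depends on assumptions. Baseline ran from June to August and endline was scheduled for February to April, so steady incidence is doubtful. That is why only a range is given. For the same reason, 5% is a limit relative to the cited figure and not a guaranteed floor for this survey.

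A reader might infer that endline teams would stop at the 120th case, leave late clusters unvisited and lose representativeness. No section states such a rule. The wording in Implementation strategy can be read as a target, and the Abstract gives its figures as approximate. A reader might also infer that the survey should be cut to about 2084 to 2778 households. Step 4 shows that this would leave only about 92 cases at the catchment's own under-five share.

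**Conclusion.** The concern holds as a wrong input to a stated sample-size figure. The 2400 children and 4167 households are derived from a 2-week prevalence, while every definition of a study case uses 28 days, and nothing in the article links the two. The word conservative in Sample size describes the 120 cases, not the prevalence.

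On the assumptions above, 2400 children correspond to about 180 to 240 cases, which is 1.5 to 2 times the stated 120. With the catchment's own under-five share, 4167 households correspond to about 138 to 184. The window error makes the survey larger than 120 cases require. It does not bias the coverage estimate or reduce its precision, and the article does not support a claim that the sample would be cut short.

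**What to change.** - In the Abstract and both paragraphs of Sample size, restate the expected case yield from a 28-day prevalence with its source. The completed 2023 baseline survey can supply it as cases per child screened, with a range for season. Use the 9.2% under-five share in the same calculation, not the prevalence alone.
- Alternatively, state that 5% is a 2-week figure kept as a cautious lower bound. In that case also report that, at a 9.2% share, 5% gives about 92 cases from 4167 households.
- Keep the 28-day window in all surveys. A 2-week window at endline would not be comparable with the 28-day baseline.
- Reconcile Implementation strategy with the Abstract and Sample size by stating that all pre-selected households are surveyed and all eligible cases analysed, whatever the running count.

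The cost is one recalculation and a few sentences. Endline was scheduled for February to April 2025 and the article is dated July 2025. If fieldwork is complete, the correction belongs in the report of results, with the numbers of households, children screened and cases actually found.

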**Figure 2 F2:**
[figure not shown]
Sample size estimation.

The total number of children to be surveyed is calculated based on a prevalence rate of 5%, resulting in an estimated sample size of 2400.^5^ Considering the proportion of 5-year-olds in the population (12% based on census data) and the average household size (4.8 as per the NFHS 5 report for Haryana), the number of households to be covered is calculated as 4167 households.^17^ These households will be selected using Probability Proportional to Size (PPS) sampling methods from the defined study area served by the 10 HWCs.^18^ Since community-level healthcare workers maintain a list of under-five children in each household, systematic random sampling will be used to select children within the chosen households.

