**Method and analysis:**

This implementation study uses a quasi-experimental pre-post design and a mixed-methods approach, conducted in three phases: (i) formative research, (ii) model optimisation through iterative testing in a learning block and (iii) scale-up and concurrent evaluation. The study is set in Palwal district, Haryana, and the primary catchment/study area will be the Health and Wellness Centres, the most accessible public health facilities for the community. Approximately 4167 households will be surveyed to capture ~2400 under-five children, among whom about 120 pneumonia cases (based on an estimated 5% prevalence) will be included in the analysis of treatment coverage and outcomes. Quantitative data will be analysed using descriptive statistics and generalised linear models, while qualitative data from focus group discussions and in-depth interviews will be thematically analysed using NVivo software.

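### The 4167-household figure rests on the district's 12% under-five share, but the sampled catchment is 9.2% under five on the protocol's own figures, giving about 1842 children and, at the plan's 5%, about 92 cases

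*Protocol article*

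**What the plan says.** The Sample size section sets the target at pneumonia cases, per survey: "a conservative sample size of 120 is to be included". It introduces the figure with the words "To account for potential non-response and to estimate 80% coverage of appropriate treatment at baseline and end-line surveys", so the 120 is presented as already containing an allowance for non-response. No rate is given, and neither is the number before the allowance.

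The same section divides by a prevalence of 5% to reach 2400 children. It then uses an under-five share of 12% and a household size of 4.8 to conclude that "the number of households to be covered is calculated as 4167 households". The 5% is described there as a prevalence over the last 2 weeks. The households come from the area served by the ten HWCs, not from the whole district.

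The Study setting section gives 12% as the under-five share of the district. For the study catchment it gives a separate count: the area "will have an estimated population of 1,07,440, consisting of 42 villages and 9897 under-five populations".

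The role of 120 varies by section. In the abstract, "about 120 pneumonia cases (based on an estimated 5% prevalence) will be included in the analysis of treatment coverage and outcomes". In Implementation strategy, the endline survey is to proceed by "using PPS sampling to identify 120 under-five children who had pneumonia symptoms in the past 28 days".

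**The concern.** The household count is only as good as the under-five share behind it, and the document gives two shares. The one used describes the district. The one implied by the catchment count describes the population that will actually be sampled, and it is about a quarter lower. If the catchment count is right, 4167 households cannot be expected to contain 2400 under-fives.

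The cases found in these households are the denominator of the primary outcome, and success is judged against a fixed threshold of at least 80% coverage. What is at stake is therefore the precision of the baseline and endline coverage estimates, together with the accuracy of three headline numbers (4167, 2400 and 120) repeated in the abstract.

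**Working it through.** **Inputs.** Sample size section: 120 cases, 5% prevalence (2-week), 12% under-five share, 4.8 people per household. Study setting section: 107,440 people and 9897 under-fives in the catchment. Operational definitions, and Description and tracking process of study outcomes: 28-day recall window.

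**1. The plan's own figure.**
- Children = cases / prevalence = 120 / 0.05 = 2400.
- Under-fives per household = 0.12 x 4.8 = 0.576.
- Households = 2400 / 0.576 = 4166.7, rounded to 4167. This matches exactly, so the inputs are not in doubt.

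**2. The share in the sampled area.**
- 9897 / 107,440 = 0.0921, or 9.2%.
- At 12% the same area would hold 0.12 x 107,440 = 12,893 under-fives, not 9897. The two figures cannot both describe the catchment.

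**3. Yield of 4167 households at 9.2%.**
- Under-fives per household = 0.0921 x 4.8 = 0.442.
- Children = 4167 x 0.442 = 1842, against 2400.
- Cases at 5% = 1842 x 0.05 = 92, against 120, a shortfall of 23%.
- Households needed for 2400 children = 2400 / 0.442 = 5428.

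**4. Precision at 80% coverage** (simple random sampling, no design effect), half-width = 1.96 x sqrt(0.8 x 0.2 / n).
- n = 120: 7.2 points.
- n = 92: 8.2 points.

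**5. The recall window.**
- The 28-day prevalence that gives 120 cases from 1842 children is 120 / 1842 = 6.5%.
- The document gives no 28-day prevalence. As an assumed range, take the 2-week 5% as the lower end (no gain from the longer window) and double it, 10%, as the upper end. Then 1842 children yield between 92 and 184 cases.

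**6. Comparison with baseline.** For the planned contrast of 25% with 80%, power at 92 cases per survey is close to 100% under simple random sampling, as it is at 120.

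**The case against.** The strongest objection is that 9.2% need not be the right share. The Study setting section gives a district birth rate of 25 per 1000. Five birth cohorts make 125 per 1000, and allowing for under-five deaths at the national 41.9 per 1000 live births leaves 0.125 x (1 - 0.0419) = 0.12. So 12% fits the district figures, assuming a roughly stable population without net migration. The catchment population is labelled an estimate, and 9897 could be an undercount. This stands as far as it goes: the document does not settle which share is correct. It does not remove the contradiction, because the plan gives a count for the area it samples and then sizes the survey with a different figure.

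The second objection is that the case shortfall appears only if the share is corrected and the 2-week prevalence is kept. This also stands. A reader might infer that the study must recruit up to 5428 households, but the documents do not support that. With a 28-day prevalence of 6.5% or more, 4167 households give 120 cases.

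Two further inferences are tempting and should not be drawn.
- A reader might conclude that non-response was ignored, because neither conversion step carries an inflation factor. The Sample size section says the 120 already accounts for it, the 92 contains no non-response term, and subtracting refusals from 92 could count the allowance twice.
- A reader might also conclude that the yield falls again because "systematic random sampling will be used to select children within the chosen households". No selection fraction is given, so no loss can be calculated.

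Finally, the abstract words its numbers as approximate, and Figure 2, which holds the sample-size estimates, is not shown. It therefore cannot be said that 92 falls below the number required before the allowance.

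**Conclusion.** The point holds as an inconsistency between inputs. On the catchment's own count, 4167 households contain about 1842 under-fives, 23% below the stated 2400. That result depends only on the 9.2% share, on 4.8 people per household and on taking every under-five in each household, as the plan's formula does. The corresponding 92 cases also require the plan's 5% to hold over 28 days, which is doubtful because it was reported for 2 weeks. The two input errors act in opposite directions and may cancel for cases, but the stated number of children is still not reached.

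The practical effect is modest: about one percentage point of half-width at 80% coverage if 92 cases are found, and no threat to detecting a change from 25% to 80% under simple random sampling.

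Separately, the Sample size section (120 includes a non-response allowance) and the abstract (about 120 analysed) do not agree. If the allowance is inside the 120, fewer than 120 are expected in the analysis.

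**What to change.** In the Sample size section:
- Reconcile the 12% with the 9897 under-fives in 107,440 people, and say which applies to the sampled area and why. Baseline data were collected in June to August 2023 according to Study status, so the number of under-fives found per household visited, if recorded, would help decide.
- Recompute with that share and with a prevalence for the 28-day window, stating its source or giving a range.
- Restate the expected children, cases and precision for 4167 households, and carry the same figures into the abstract.
- Say once whether 120 is the number of cases found, with the non-response allowance and its rate, or the number analysed, and use that meaning in the abstract and in Implementation strategy.

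The cost is a few sentences and one recalculation. No change to the number of households or to the way children are selected follows from this point. Altering selection at endline alone could weaken comparability with the baseline survey. As the endline survey is scheduled for February to April 2025, the results report should set expected against achieved children, cases and precision for each survey.
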